#### Analysis

##### Sample size calculations

A sample of 244 families will provide greater than 99% power in finding an increase from the current service utilisation of 30% doubling it to 60% in the intervention group with statistical significance at 5%. Taking non- and partial-adherence and sample dropout into account at 5%, the required sample size was revised to 300 (150 per group)*.*

##### Statistical analysis

A multilevel models estimated by restricted maximum likelihood (REML) with logit link function will be used to model service utilisation over the 3 time points. The main predictors of interest will be time, group and a time by group interaction which will compare service utilization between the groups at each time point. The analysis will be adjusted for the caregivers, socioeconomic status, and the main language spoken in the home.

A multilevel model estimated by restricted maximum likelihood (REML) with identity link function will be used to model the K10, WE CARE and LTSAE totals. The main predictors of interest are time, group and time by group interaction. The analysis will be adjusted for the caregivers, socioeconomic status, and the main language spoken in the home.

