##### Assessments

All participants will complete consent forms and a demographic information questionnaire along with the study questionnaires through the REDCap platform. These questionnaires will be made available in English, Vietnamese, Arabic, and simplified Chinese (the four most common languages spoken in NSW). Where translated versions of questionnaires exist, they will be used, otherwise a licensed interpreter will be commissioned to translate the questionnaires during assessment. Those who cannot speak English will be linked up with services with access to interpreters as part of their service delivery. The demographic questionnaire, which will be completed at trial entry (baseline), will include the child’s date of birth, the child’s gender, whether the child was born premature, the child’s country of birth, the mother’s age, the mothers education level, the mother’s country of birth, the fathers age, fathers education level, the father’s country of birth, parent marital status, socioeconomic status, and the main language spoken in the home. The study questionnaires will be completed at three time points: baseline [Time 1], six-months post-intervention [Time 2], and 12-months post-intervention [Time 3]. See Figs. 1 and 2 for a summary of participant flow through the study.

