##### Service utilisation

As a way to track participants service utilisation, participants will be asked to complete a questionnaire, developed by the researchers, about the services that they are accessing. The following questions are included in the questionnaire: Do you or your child currently attend any health services? (question 1); if participants indicate ‘Yes’ on question 1, they will also be asked: Do you and/or your child currently attend any of the following services? (Psychologist, Social worker, Paediatrician, Occupational therapist, Speech pathologist, Early childhood education/intervention centres, Other) (question 2); who is receiving this service (you, your child, both)? (question 3); when did you/your child begin attending the service/s? (question 4); and how frequently do you/your child attend the service (e.g., weekly, monthly)? (question 5).

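### REML has no exact counterpart for the logit-link model of service utilisation; fitted as a linearised pseudo-likelihood, it would shrink the conditional odds ratio, and its interval can under-cover

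*Protocol article*

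**What the plan says.** The Statistical analysis section of the protocol article specifies, for service utilisation, a multilevel model "estimated by restricted maximum likelihood (REML) with logit link function will be used to model service utilisation" over three time points. The terms of interest are time, group and "a time by group interaction which will compare service utilization between the groups at each time point". The following paragraph uses nearly the same sentence, with an identity link, for the K10, WE CARE and LTSAE totals.

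The outcome is binary: the Service utilisation section opens with a yes/no question, "Do you or your child currently attend any health services". Each family contributes at most three records, since "The study questionnaires will be completed at three time points" (Assessments section). The sample size rests on this outcome alone: an "increase from the current service utilisation of 30% doubling it to 60% in the intervention group".

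The article names no integral approximation, pseudo-likelihood variant or software for the logit model. It gives no within-family correlation and does not say whether the odds ratio is meant to be conditional on the family or marginal.

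**The concern.** REML is the likelihood of error contrasts in a linear model with normal errors. It suits the identity-link models. For a binary outcome with a logit link and random effects there is no exact equivalent. Software that offers REML in that setting typically linearises the model and applies REML to the working response (penalised quasi-likelihood or residual pseudo-likelihood). That approximation is weakest with binary data and few records per cluster, which is the situation here.

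What is at stake is the reported size of the navigator's effect on the outcome for which the trial was sized, together with its confidence interval. If the software also estimates a residual scale, the interaction test may be affected as well.

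**Working it through.** **Inputs from the article.** 244 families before inflation and 300 after; 1:1 allocation; three records per family; 30% vs 60%; 5% significance (sidedness not stated, two-sided assumed).

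**Input assumed.** The family random-intercept SD on the logit scale, s, varied from 0.5 to 3. The latent intraclass correlation is s²/(s² + π²/3), for example 1/(1 + 3.29) = 0.23 at s = 1.

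**Step 1: the plan's own figure.** The article states that "A sample of 244 families will provide greater than 99% power". With 122 per arm, the standard error is √(2 × 0.45 × 0.55/122) = 0.0637 under the null and √((0.21 + 0.24)/122) = 0.0607 under the alternative. Power is Φ((0.30 − 1.96 × 0.0637)/0.0607) = Φ(2.88) = 99.8%. The stated power reproduces.

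**Step 2: the two possible targets.** The marginal log odds ratio is ln(0.6/0.4) − ln(0.3/0.7) = 0.405 + 0.847 = 1.253. The conditional log odds ratio that yields the same 30% and 60% after averaging over families is larger and grows with s (table).

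**Step 3: simulation.** Data came from a random-intercept logistic model with 30% in both arms at baseline, then 30% vs 60% at Times 2 and 3, with no missing data and no covariates. Each cell had 250 to 800 replicates, so the Monte Carlo standard error of coverage is about 1 to 2.5 points. Results for restricted pseudo-likelihood, residual scale fixed at 1, N = 300, Time 2 group contrast against the conditional value:

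| s | Latent ICC | True conditional log OR | Bias | 95% CI coverage |
|---|---|---|---|---|
| 0.5 | 0.07 | 1.324 | −4.1% | 93.2% |
| 1 | 0.23 | 1.508 | −13.3% | 88.8% |
| 1.5 | 0.41 | 1.760 | −22.1% | 70.8% |
| 2 | 0.55 | 2.052 | −29.6% | 46.0% |
| 3 | 0.73 | 2.703 | −41.8% | 5.8% |

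Repeat runs at s = 0.5 to 2 gave bias of −5%, −13%, −22% and −30% and coverage of 95%, 89%, 71% and 45%. At s = 2 the mean estimate is 1.444 against 2.052, an odds ratio of e^1.444 = 4.2 instead of e^2.052 = 7.8. The ratio of empirical to model standard error was 0.88 to 1.03, so the under-coverage comes from the bias and not from standard errors that are too small.

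**Step 4: where the harm is absent (scale fixed).** For 30% vs 45% at s = 1, bias was −11.1% but coverage 94.6%. Under no effect, at s = 1, 2 and 3, coverage was 96.2%, 97.2% and 96.2%, and type I error for the Time 2 contrast 3.8%, 2.8% and 3.8%. At 30% vs 60%, power for the Time 2 contrast stayed at or above 99.6%.

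**Step 5: residual scale estimated instead (N = 300, s = 1, 2, 3).** Time 2 bias was −8.0%, −11.8% and −12.8%; coverage was 92.4%, 82.4% and 79.2%. Under no effect, type I error for the time-by-group interaction was 5.0%, 14.7% and 19.7%.

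**Step 6: the alternative estimator.** Full maximum likelihood by Gauss-Hermite quadrature, N = 300, s = 0.5, 1, 1.5: bias +1.3%, +1.1%, +1.2%; coverage 93.6%, 95.2%, 94.4%. N = 244, s = 2, 3: bias −0.3%, +3.5%; coverage 94.2%, 95.6%.

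**The case against.** **The algorithm is inferred.** The article names neither pseudo-likelihood nor software, and REML may be wording carried over from the linear models. This stands: the consequences depend on how the sentence is implemented. It does not remove the point, because the article does name an estimator, and the one it names does not fit this outcome. That differs from leaving a detail to the SAP.

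**Under-coverage is not general.** A reader might infer that the planned intervals under-cover whatever the data. The documents do not support that. They give no family variance, and coverage is close to nominal at s = 0.5, for a smaller effect at s = 1, and under no effect with the scale fixed. A large s is plausible, since current attendance at any service is likely to persist within a family, but it remains an assumption.

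**The yardstick is the conditional odds ratio, which the article never names as its target.** Against the marginal 1.253, the same intervals (scale fixed, s up to 2) cover about 90% to 96% of the time. A GEE, offered below as an alternative, differs from the conditional value by more than pseudo-likelihood does: 1 − 1.253/2.052 = 39% at s = 2, against 30%. This stands as a limit on the claim. The two cases are not alike, however. A GEE estimates a defined marginal quantity. The pseudo-likelihood estimate falls between the two targets: at s = 2 it is 1.444, below 2.052 and 1.444/1.253 − 1 = 15% above the marginal value. Its near-coverage of 1.253 is accidental, and falls to 88% at s = 3.

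**The main test survives.** A reader might infer that the trial loses power or that its test is invalid. With the scale fixed, neither is so. Nor is there a case that likelihood-ratio tests would be invalid, since the article plans none.

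**Conclusion.** The point holds in limited form. Pairing REML with a logit link does not specify a valid estimator for service utilisation, and this follows from the article's text alone.

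The numerical consequences rest on four assumptions: a linearised pseudo-likelihood fit, the conditional odds ratio as target, the article's 30% vs 60%, and an assumed family SD. Under these, with N = 300 and the scale fixed, the group log odds ratio is shrunk by about 4-5% at s = 0.5, rising to 30% at s = 2, and coverage falls from 93-95% to 45-46%. The harm is then to the reported effect size and interval; power and type I error are not at issue. If the scale is estimated, the shrinkage is smaller (about 8% to 13%), but the interaction test can reject too often at large SD. The article leaves open which variant would be used. The correction should be made, but it is not a reason to doubt the design.

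**What to change.** For service utilisation, replace the REML wording with a logistic mixed model with a family random intercept, fitted by maximum likelihood with adaptive Gauss-Hermite quadrature. Report the standardised (marginal) risk difference at Time 2 alongside the odds ratio, because that is the scale on which 30% vs 60% was planned. A logistic GEE with robust standard errors is an acceptable alternative, provided its odds ratio is stated to be marginal. Keep REML for the K10, WE CARE and LTSAE models.

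The cost is one sentence in the analysis plan and one software option; no change to data collection or sample size is needed.

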#### Participants

Participants will include 300 parents/caregivers (150 from Fairfield Local Government Area (LGA) and 150 from Murrumbidgee Local Health District (LHD)) of children aged 6 months to 3 years (inclusive).

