#### Setting

Fairfield (population: 198,817; 102 km^2^) [24] is an urban area and has a high proportion of CALD families, with about 70% of residents speaking a language other than English at home [24]. Murrumbidgee LHD (population: 77,652; 125,242 km^2^) [24] is considered mostly regional with one remote area making access to health care a challenge for most families with young children.

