##### Economic analysis

Economic evaluation will assess the cost effectiveness (cost utility) of the intervention against usual care. Costs will include the care coordinator for the intervention group and the costs of completed service referrals for both trial arm. Effectiveness will be measured by converting K-10 scores into utilities using a mapping algorithm that converts scores to EQ-5D values [29]. REML will also be applied to assess significant changes in costs and outcomes. An Incremental Cost Effectiveness Ratio (ICER) will then be generated with values $42,000–$67,000 considered to be cost effective [30]. Implementation costs from roll-out will be estimated, including the eligible population size, the number of service coordinators required and service referrals. Sensitivity analysis will then vary key parameters such as service uptake and a threshold analysis will estimate the minimum service engagement required to maintain cost effectiveness in implementation. A value of information analysis will estimate statistical uncertainty and the potential value from further research to optimize implementation.

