## Discussion

Families from disadvantaged backgrounds face a fragmented health system with financial, social, and structural barriers. Even when services are available, engagement and access to services are compounded by cultural and linguistic barriers as well as geographic challenges. These are exacerbated by the pandemic and the consequent impact on in-person services.

This study will address these challenges by testing the WMG-E web-app as a digital navigation tool to engage parents at home or through opportunistic contacts with health, early childhood education or other community/social care services. Extending earlier research using WMG-E to engage parents in developmental monitoring [35], this study will include parental mental health and psychosocial needs, alongside child developmental needs. Thus, this study will test the acceptability, effectiveness, and cost-effectiveness of WMG-E for families of children aged 6 months to 3 years (inclusive) in a predominantly CALD community and a regional/rural community to increase engagement of families with services and better identification of their needs.

Furthermore, this study will specifically evaluate whether a service navigator will increase family wellbeing by facilitating access to relevant services. Families in the intervention group are expected to experience significantly improved parental mental health, psychosocial wellbeing, and development outcomes compared to the control group. By targeting CALD and rural/regional communities, we will demonstrate the feasibility of the WMG-E for the most vulnerable and disadvantaged families. Following this, the online platform will be ready for national implementation with potential for international adaptation.

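### The stated models and the single ICER average over two deliberately contrasting communities, and no stated analysis shows whether the navigator's effect differs between them

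*Protocol article*

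**What the plan says.** The Participants section fixes 150 families from each of two areas. The Setting section describes them as very different: Fairfield is urban, covers 102 km², and about 70% of residents speak a language other than English at home; Murrumbidgee covers 125,242 km² and is mostly regional with one remote area, "making access to health care a challenge for most families with young children". The Discussion says acceptability, effectiveness and cost-effectiveness will be tested "in a predominantly CALD community and a regional/rural community", and goes on to national implementation.

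For service utilisation, the Statistical analysis section states: "The main predictors of interest will be time, group and a time by group interaction". The model for K10, WE CARE and LTSAE has the same terms. Both are adjusted for caregivers, socioeconomic status and home language. Site appears neither as a main effect nor in an interaction, and no by-site estimate is named. The Economic analysis section generates one ICER and adds: "Implementation costs from roll-out will be estimated, including the eligible population size". Its sensitivity analysis names service uptake as a parameter to vary; it does not name community.

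**The concern.** The navigator acts by connecting families to services in their local area, with in-person assessment and a supported hand-over for those at high risk. How much that can achieve plausibly depends on which services exist nearby and how far away they are, and this is where the two settings differ most. A different effect at each site is therefore a realistic possibility on the protocol's own description.

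The stated models give a group difference at each time point, averaged over the two sites with roughly equal weight because of the recruitment quota. That average does not show whether the two effects are alike. Adjusting for language and socioeconomic status shifts the level of the outcome and leaves a single treatment effect. The models are called multilevel without saying what the levels are; if site were one of them, a random intercept would also leave one averaged effect. The interviews in Phase 2 recruit at both sites but estimate no effects.

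At stake is the reading of the result. A reader who sees a significant pooled effect beside a Discussion that speaks of both communities may take it to hold in each, with no stated estimate to check against.

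**Working it through.** **Inputs.** From Sample size calculations: "finding an increase from the current service utilisation of 30% doubling it to 60% in the intervention group", a 5% significance level, 244 families (122 per arm), raised to 300 (150 per arm). From Participants: half the families from each site. Assumed here: a two-sided test; 1:1 allocation within site (the Randomisation section states 1:1 overall only), hence 61 to 75 per arm per site; a single time point without repeated measures or covariates; and 30% control utilisation at both sites, since the article gives no site-specific rates.

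**Formula.** Power = Φ{[d − 1.96·√(2·p̄(1−p̄)/n)] / √([p₁(1−p₁)+p₂(1−p₂)]/n)}, with n per arm, d = p₂ − p₁ and p̄ the mean of the two proportions.

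**1. The plan's own figure.** 30% versus 60%, n = 122: [0.30 − 1.96·√(0.495/122)] / √(0.45/122) = (0.300 − 0.125)/0.0607 = 2.88, so power is 99.8%. This agrees with "A sample of 244 families will provide greater than 99% power".

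**2. Whole benefit at one site (illustration).** One site 30% to 60%, the other 30% to 30%. The pooled intervention rate is (60 + 30)/2 = 45%, so the contrast is 30% versus 45%: +15 points, odds ratio (0.45/0.55)/(0.30/0.70) = 1.91. The true site effects are +30 and 0.
- n = 122: (0.150 − 0.1215)/0.0612 = 0.466, power 68%.
- n = 150: (0.150 − 0.1096)/0.0552 = 0.732, power 77%.

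So 68% to 77% of such trials would show a significant average benefit, and the other 23% to 32% would miss a real 30-point gain at one site.

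**3. Precision of by-site estimates.** The half-width of a 95% interval for a risk difference is 1.96·√([p₁(1−p₁)+p₂(1−p₂)]/n).
- One site, n = 61: 16.3 points (30% vs 30%) and 16.8 points (30% vs 60%).
- One site, n = 75: 14.7 and 15.2 points.
- Pooled 30% vs 45%: 12.0 points (n = 122) and 10.8 points (n = 150).

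By-site intervals are about 1.4 times as wide as the pooled one (16.8/12.0 = 1.4). Power within one site for the full 30% to 60% is 92% (n = 61) to 97% (n = 75). For 30% to 45% within one site it is only 40% to 47%.

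**4. Interaction on the model's log-odds scale.** For +30 versus 0 points the ratio of odds ratios is 3.5, with log 1.253.
- n = 61: standard error √(3/(61·0.21) + 1/(61·0.24)) = 0.550; power Φ(1.253/0.550 − 1.96) = 62%.
- n = 75: standard error 0.496; power 71%.

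For a milder contrast (30% to 60% at one site, 30% to 45% at the other) the log ratio is ln(3.5/1.91) = 0.606, with standard errors 0.539 and 0.486, and power falls to 20% to 24%.

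**The case against.** The best defence is that the plan is consistently a pooled one. The Objectives concern families from CALD, regional and rural communities together, the hypotheses compare intervention with control, the Design is group by time, and the sample size rests on one contrast. The Discussion sentence can be read as describing where the trial is run, with no promise of an effect for each community. By-site estimates are often left to an analysis plan, which is not shown here, and listing the main predictors does not exclude others. Much of this stands: the pooled model answers the stated objectives and is not an error. What remains is that the article does spell out its predictors and covariates, and none of them can show a difference between the two communities it chose for their contrast.

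Three stronger readings might be inferred, and the documents support none of them.
- *A one-site benefit would be reported as working in both.* That predicts future reporting. Even under the assumed scenario the pooled test succeeds in only 68% to 77% of trials.
- *The 50:50 trial average will be carried into roll-out and should be re-weighted 72:28, as the populations of 198,817 and 77,652 would suggest.* Nothing says the trial average will be applied in this way. The Economic analysis already uses eligible population size, varies uptake and runs a threshold analysis. The 72:28 split counts all residents, not children aged 6 months to 3 years, and is not the weighting of a national target.
- *Effectiveness in each community should be claimed from that community's own estimate, or decided by the interaction test.* The trial was sized for one pooled contrast, and the interaction power above is too low to bear that weight.

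**Conclusion.** The point holds as a cheap improvement to an otherwise valid analysis. The stated models and the single ICER estimate averages over two contrasting communities, and no stated analysis shows whether the navigator's effect differs between them, although the Discussion frames the test as covering both. The size rests on an assumed extreme, +30 points at one site and 0 at the other from a common 30%: the pooled contrast becomes 30% versus 45%, significant in about 68% to 77% of trials. A one-site benefit could therefore be read as general, or be missed. By-site estimates would be informative if a site showed the full planned doubling, and much less so for smaller effects.

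**What to change.** Keep the pooled time-by-group effect as the main analysis and add site to the models as a fixed covariate. Pre-specify, as secondary and descriptive results, the group differences at Time 2 and Time 3 within each site for service utilisation and K10, with 95% confidence intervals, from a model that includes site-by-group-by-time terms. Report uptake and costs by site and use them as an input to the roll-out sensitivity analysis. State that a non-significant site interaction will not be taken as evidence of equal benefit.

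This needs a few lines of analysis wording and no extra families or data. The price is imprecision: about ±15 to 17 points by site for service utilisation, against about ±11 to 12 pooled. The matching precision for K10 and for costs by site cannot be worked out from the article, which gives no standard deviations.

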The proposed study will expand WMG-E by incorporating screeners for parents’ mental health and unmet psychosocial needs (e.g., financial support, housing) to optimise families’ wellbeing. Like the developmental screener, when mental health and/or unmet psychosocial risks are indicated, families will be directed to relevant resources electronically through WMG-E in the control group while the intervention group will be guided to receive more detailed assessments and provided ongoing care to ensure the uptake of recommended services. This study also aims to evaluate whether additional support through a ‘service navigator’ (i.e., WMG-E + service navigator) increases family access and uptake of services for families identified as at high-risk by WMG-E. Previous research conducted by Hughes and colleagues [13] has shown that the involvement of a service navigator can enhance families’ connections to services. The role of the service navigator, similar to that of the care coordinator in Hughes et al.’s [13] study, will be to review the parents’ mental health, psychosocial, and developmental screener results, connect them with relevant support services as needed, facilitate access and uptake of recommended services and provide continuity of care to ensure that their needs are met. Specifically, in the intervention group, the navigator will contact the family initially to discuss and clarify the concerns that were raised by the family while completing WMG-E. Once the service navigator has clarified the family’s needs, they will provide guidance to the family on available services and supports in their local area, whom to speak to at relevant agencies, specific questions to ask, and, if necessary, help complete referral forms and where needed directly link them with the service. The service navigator will then contact the family within a 2-week period to determine whether they were able to successfully engage with the available services and supports. The service navigator will continue to contact the family on a biweekly basis to check in regarding their engagement with recommended services and determine whether they have any additional concerns or unmet needs.

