## Objectives

The primary objectives of the Randomised Controlled Trial (RCT) component involving families of children aged 6 months to 3 years from CALD, regional and rural communities in NSW are to evaluate: (1) the engagement with developmental surveillance; (2) access to services for those with mental health and social care needs; and (3) uptake of service recommendations. Secondary objectives will include examining (1) the effectiveness of the WMG-E platform in identifying and addressing parental mental health, parental psychosocial and child developmental needs; and (2) whether a service navigator, in addition to the WMG-E platform, increases family wellbeing by facilitating access to relevant services and by providing continuity of care.

The objective of the implementation evaluation is to ascertain the acceptability, feasibility and the impact of the WMG-E platform and service navigator.

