### Randomised controlled trial

Using an RCT methodology we will compare a ‘care-as-usual’ (CaU) group with an intervention group. Both groups will complete parental mental health, psychosocial needs, and child developmental screeners via WMG-E. Furthermore, both groups, if risk is identified, will receive electronic resources guiding them to health services that can be accessed for more detailed assessments.

The intervention group will be provided with ongoing monitoring, via a service navigator, to ensure uptake of recommendations and access to additional support for those identified to be at risk. The service navigator will first triage intervention families based on their level of risk as indicated by the WMG-E platform which screens for developmental, parental mental health, and psychosocial risk. Participants who indicate no developmental concerns on the LTSAE and psychosocial concerns on the WE CARE questionnaire [17] and have scores lower than 20 on the Kessler Psychological Distress (K10) scale [18] will be considered low risk. Participants who indicate one or more developmental and/or psychosocial concerns and/or have scores ranging from 20 to 24 on the K10 will be considered medium risk. Participants who have scores equal to or greater than 25 on the K10 and/or indicate risks of homelessness, domestic violence, loss of electricity, or food insecurity will be considered high risk. Completing the screening tools on the WMG-E platform will take between 10 and 15 min.

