Families with lower level risks will be connected with local services and might also be provided with information on online resources (e.g., free to access online parenting programs such as ParentWorks [19] or Movember Family Man [20]) or therapist-assisted interventions (e.g., online or in-person Parent-Child Interaction Therapy [21]). For families who are at high risk, in addition to receiving resources and linkages to services as mentioned above, they will receive in-person assessments (through a KIDS-Connect hub [22] with capacity to reach families at homes or other community facilities) to determine the complexity of health needs followed by appropriate referrals and a ‘warm hand-over’ (i.e., directly linking patients to services in a supportive manner) to recommended services. The duration of in-person (or digital as indicated in extreme circumstances) assessments will depend on the needs identified by the WMG-E, however, these assessments generally range from 30 to 60 min [22]. Once the in-person assessment is completed and families are linked with recommended services, the type and duration of services they receive will depend on their needs. For example, families with psychological needs may receive ten 60-min sessions with a psychologist while families with unmet psychosocial needs who access services such as Uniting (community service agency) [22, 23] may receive 2–3 sessions targeted at addressing psychosocial needs. Furthermore, these families will receive follow-up support by the navigator to ensure engagement with recommended services and continuity of care. Follow-ups will occur fortnightly via telephone for a duration of 10 to 20 min.

We hypothesise that in the first 6 months, the intervention group will have better access and engagement with services due to this group not only getting linked up with services but also continuity of care through the service navigator to ensure the uptake of recommended services. Further we hypothesize that, families in the intervention group that are connected with services will also show a significantly greater increase in wellbeing relative to the control group, at the 12 month follow up. This is because, via the service navigator, they will have assistance in connecting with services and ongoing monitoring and support to ensure that their needs are being met.

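### The service-use comparison is neither restricted to nor adjusted for Time 1 risk, although primary objectives 2 and 3 concern families with needs or recommendations, and the 30% and 60% rates are not tied to a population

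*Protocol article*

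**What the plan says.** All references are to the protocol article.

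- **Objectives.** There are three primary objectives. The first, engagement with developmental surveillance, is not limited by need. The second is "access to services for those with mental health and social care needs". The third is uptake of service recommendations, which presupposes that something was recommended.
- **Randomised controlled trial.** Navigator monitoring is "to ensure uptake of recommendations and access to additional support for those identified to be at risk". The section defines a low-risk group: no developmental concern, no psychosocial concern and a K10 score below 20.
- **Participants; Recruitment.** Neither section makes an identified need a condition of entry.
- **Service utilisation.** The questionnaire first asks about current attendance at any health service. It does not link attendance to a need or a recommendation.
- **Statistical analysis.** The model contains time, group and "a time by group interaction which will compare service utilization between the groups at each time point". The covariates named are the caregivers, socioeconomic status and main home language. Risk level is not among them.
- **Sample size calculations.** "A sample of 244 families will provide greater than 99% power" for "finding an increase from the current service utilisation of 30% doubling it to 60% in the intervention group". The families to whom the two rates apply are not specified.

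The article also varies on who gets the navigator. Background sets out to test whether the navigator "increases family access and uptake of services for families identified as at high-risk by WMG-E", then describes contact with intervention families generally. Under Randomised controlled trial, support is for those at risk, but the sentence "these families will receive follow-up support by the navigator to ensure engagement with recommended services and continuity of care" follows text on high-risk families. Under Intervention group, participants' results go to the navigator, and families who do not engage are counted as dropouts.

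**The concern.** A family with no concern on any screener has no risk-based reason to start a service. In the planned comparison, its non-attendance counts the same as that of a family with an unmet need. If the navigator works mainly in families with needs, the between-arm difference is an average over families in whom an effect is expected and families in whom little is expected.

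Two things are at stake. The estimate would not answer objectives 2 and 3 as worded. And a real effect in families with needs could be missed if the 30% and 60% were meant for those families, because the power was calculated as if they held for the whole arm.

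**Working it through.** **Inputs.** From Sample size calculations: 30% v 60%, 5% significance (two-sided assumed, as sidedness is not stated), 244 families, 300 randomised (150 per arm), 5% loss. From Randomisation: 1:1 allocation, so 122 per arm. The at-risk share *s* is not given and is an assumption throughout.

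**Formula.** Power = Φ[(Δ − 1.96·SE₀)/SE₁], with SE₀ = √(2p̄(1−p̄)/n) and SE₁ = √([p₁(1−p₁) + p₂(1−p₂)]/n).

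**1. The plan's own figure.** With n = 122, p₁ = 0.30, p₂ = 0.60 and p̄ = 0.45, SE₀ = 0.0637 and SE₁ = 0.0607. Then (0.30 − 1.96 × 0.0637)/0.0607 = 2.88, and power is 99.8%. The claim of more than 99% is reproduced.

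**2. Gain confined to the at-risk share.** Assume 30% in all control families and in low-risk intervention families, and 60% in at-risk intervention families. The intervention arm then averages 0.30 + 0.30·s. The calculation is done at 122 per arm and at 142 per arm (150 × 0.95 = 142.5).

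**3. At-risk families only.** 30% v 60% with 122·s per arm, assuming equal retention.

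| s | Arm-wide rates | Whole arm, 122 | Whole arm, 142 | At-risk only (n per arm, from 122) |
|---|---|---|---|---|
| 0.8 | 30% v 54% | 97% | 99% | 99% (98) |
| 0.6 | 30% v 48% | 83% | 88% | 96% (73) |
| 0.4 | 30% v 42% | 50% | 56% | 86% (49) |

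Under this assumption, whole-arm power exceeds 99% only if s is at least about 0.89 with 122 per arm, or 0.82 with 142. It exceeds 80% if s is at least about 0.58 or 0.54.

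**4. Lower base rate in low-risk families.** At s = 0.5 and 122 per arm, a low-risk rate of 30%, 20% or 10% gives arm-wide rates of 30% v 45%, 25% v 40% or 20% v 35%, and power of 68%, 71% or 75%. The conclusion does not change.

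**5. Unequal retention.** Recruitment excludes families in acute crisis if they are allocated to control, on criteria close to those for high risk. Intervention group counts families who do not engage with the navigator as dropouts. Suppose 40% of families are at risk and 20% are high risk, and the high-risk families are lost from control only. The at-risk comparison then has 122 × 0.4 ≈ 49 intervention families and 122 × (0.4 − 0.2) ≈ 24 controls. With p̄ = (24 × 0.3 + 49 × 0.6)/73 = 0.501, SE₀ = √(0.25 × (1/24 + 1/49)) = 0.1246 and SE₁ = √(0.21/24 + 0.24/49) = 0.1168. Then (0.30 − 1.96 × 0.1246)/0.1168 = 0.48, and power is about 68% instead of 86%. The remaining controls would also be the less needy ones, so the comparison would be biased as well as small.

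**The case against.** A reader might infer that the stated power is wrong. The article does not support that. The figure reproduces, and 60% in the intervention group can be read as an arm-wide rate with low-risk families already averaged in; there is then no further dilution. A high at-risk share is also plausible, since one concern is enough for medium risk and recruitment includes refugee health and special paediatric clinics. This stands, so the power loss is conditional.

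A reader might also infer that low-risk families cannot benefit. That is too strong. Families with lower-level risks are to be connected with local services, repeated contact may bring out new needs, and the questionnaire covers any health service. Zero effect in low-risk families is an assumption of the calculation.

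Nor does the article say that every randomised family is analysed. It names no analysis population, which a condensed article may leave to the full protocol or analysis plan, and its dropout rules point the other way. Objective 1 and a platform offered to everyone also make a whole-arm comparison a legitimate question.

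Finally, it is tempting to say that restricting to at-risk families is free of selection bias because risk is measured before randomisation. The definition is unbiased, but the one-sided dropout rules act mainly within that subset, so the assurance fails unless those families are kept.

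What remains is the mismatch in the text: objectives 2 and 3 concern families with needs or recommendations, and the model that lists its own covariates takes no account of need.

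**Conclusion.** The point holds as a mismatch between primary objectives 2 and 3 and the stated comparison of service use, together with a power statement whose population is undefined. It does not hold as an arithmetic error in the power.

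The size depends on two things the article does not give: which families the 30% and 60% describe, and the at-risk share. If 60% is arm-wide, power is as stated. If the gain is confined to at-risk families, the loss is small at a share of 80% (97% with 122 per arm, 99% with 142) and serious at 40% (50% and 56%). With equal retention, an at-risk comparison loses less power despite its smaller sample. That advantage is not assured if the arm-specific dropout rules carry through to the analysis.

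**What to change.** 1. For objectives 2 and 3, make the main comparison the families flagged at risk at Time 1, using the same pre-randomisation definition in both arms. Keep objective 1 in all families.
2. Report service use in all families as well, with Time 1 risk level as a covariate.
3. State which families the 30% and 60% describe, and give power over a range of at-risk shares.
4. For this comparison, keep in the analysis, as randomised, the control families in acute crisis and the intervention families who do not engage with the navigator.
5. Reconcile Background, Randomised controlled trial and Intervention group on which intervention families receive the navigator and its follow-up.

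**Cost.** Items 1 to 3 need wording and one recalculation; Time 1 screening is already collected in both arms. Item 4 requires Time 2 and Time 3 questionnaires from families now treated as dropouts. The main downside is fewer families in the main access comparison: about 98, 73 or 49 per arm out of 122 for shares of 80%, 60% or 40%.
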